# Comparing systemic therapy and cognitive behavioral therapy for social anxiety disorders: study protocol for a randomized controlled pilot trial

**DOI:** 10.1186/s13063-016-1252-1

**Published:** 2016-03-31

**Keywords:** Systemic therapy, Cognitive behavioral therapy, Social anxiety disorder, Adherence, Randomized controlled trial (RCT), Pilot, Manual development

## Abstract

**Background:**

Social anxiety disorders are among the most prevalent anxiety disorders in the general population. The efficacy of cognitive behavioral therapy (CBT) for social anxiety disorders is well demonstrated. However, only three studies point to the efficacy of systemic therapy (ST) in anxiety disorders, and only two of them especially focus on social anxiety disorders. These ST studies either do not use a good comparator but minimal supportive therapy, they do not use a multi-person ST but a combined therapy, or they do not especially focus on social anxiety disorders but mood and anxiety disorders in general. Though ST was approved as evidence based in Germany for a variety of disorders in 2008, evidence did not include anxiety disorders. This is the first pilot study that will investigate multi-person ST, integrating a broad range of systemic methods, specifically for social anxiety disorders and that will compare ST to the "gold standard" CBT.

**Design:**

This article describes the rationale and protocol of a prospective, open, interventive, balanced, bi-centric, pilot randomized controlled trial (RCT). A total of 32 patients with a primary SCID diagnosis of social anxiety disorder will be randomized to either CBT or ST. Both treatments will be manualized.

The primary outcome will include social anxiety symptoms at the end of therapy. Therapy will be restricted to no more than 26 hours (primary endpoint). Secondary outcomes will include psychological, social systems and interpersonal functioning, symptom adjustment, and caregiver burden, in addition to change measures, therapist variables and treatment adherence. At the secondary endpoints, 9 and 12 months after the beginning of therapy, we will again assess all outcomes.

**Discussion:**

The study is expected to pilot test a RCT which will be the first to directly compare CBT and multi-person ST, integrating a broad range of systemic methods, for social anxiety disorders, and it will provide empirical evidence for the calculation of the number of patients needed for a confirmatory RCT.

**Trial registration:**

ClinicalTrials.gov: NCT02360033; date of registration: 21 January 2015.

## Background

Both cognitive behavioral therapy (CBT) and systemic therapy (ST) have a long tradition in the psychotherapeutic treatment of various disorders. However, CBT has a much stronger history of manualization and evaluation, especially for patients with anxiety disorders [1]. It is also part of insurance-funded German psychotherapy, which ST is not. ST was approved as evidence based in Germany for a variety of disorders, but evidence did not include anxiety disorders [2, 3]. Three randomized controlled trials (RCTs) for anxiety disorders are available [4–6]. However, they either do not especially focus on social anxiety disorders but mood and anxiety disorders in general [4], they do not use a multi-person ST but a combined therapy [5], or they do not use a "gold standard" comparator but minimal supportive therapy (MST) [6]. We therefore need more studies that investigate the efficacy of ST specifically for social anxiety disorders, and that use a multi-person ST compared to a well-investigated comparator, such as CBT.

### Epidemiology

Social anxiety disorders are among the most prevalent anxiety disorders (prevalence of 7–16 %). In general, women are affected more frequently (3:2) [7]. In clinical populations, we find women and men in equal shares [8]. Both women and men are affected by the many significant psychosocial and occupational limitations that accompany social anxiety disorders [9]. Those affected have lower income and education, higher unemployment, are more often unmarried and have fewer friends [10]. The age of onset of social anxiety disorders averages 10–13 years [7]; spontaneous remission in the first 2 years is below 20 % [11, 12].

### Clinical picture

Social anxiety disorders are interpersonal disorders. Symptoms of fear such as shaking or flushing arise when the affected person experiences that he or she may attract attention, and that symptoms such as shaking or flushing constrain his or her ability to build up social relationships [13]. Socially anxious individuals display little emotionality, intimacy and secure bonding [14]. The performance anxiety type describes, for example, fears being seized with stage fright, behaving awkwardly if aware of being scrutinized by others and/or getting flurried in larger groups when speaking publicly or eating in restaurants. The interpersonally anxiety type describes, for example, fear of giving an impression of being a bore, an odd fellow and/or difficult to get along with so that the individual is the only one out of keeping with company in everyday situations in medium-sized groups, for example, during lunch with work colleagues or at a garden party with neighbors [15]. People with the specific subtype fear to speak or to eat in public in some specific social situations. Individuals with the generalized subtype fear such behavior in a greater number of situations. The generalized subtype shows stronger burden caused by the generalized socially anxious symptomatology and by more severe comorbidity [7].

### Psychotherapy

CBT explains the disposition of social anxiety disorders by cognitive schemas which stimulate misleading internal information processing. Socially anxious individuals show increased self-focused attention when interacting with others stimulated by the assumption that others can see their anxiety. Based on a linked reduction in observation of other people, they focus on negative reactions and tend to interpret ambiguous and neutral feedback in a negative way. This results in excessively negative inferences about how they appear to others. Incorrect cognitions induce avoidance of social situations and/or the extensive use of safety behavior (e.g. avoiding eye contact, speaking low). The intention is on the prevention of feared catastrophes. However, avoidance and safety behavior contributes to the maintenance of negative beliefs and the increase of feared symptoms. They make patients come across to others in ways that are likely to elicit less friendly responses [8, 16, 17].

CBT aims to reverse the maintaining processes specified in the cognitive model of Clark and Wells [17]. The goal is to establish a realistic self-perception. The CBT manual [8] differentiates between five phases which are described in detail in the method section.

ST explains the development of social anxiety disorders by reciprocal interpersonal interactions. Symptoms of social anxiety serve the near-distance regulation when interacting with others. They represent the (non-verbal) communication of dyadic or multi-person “between-us” quality of relationship in private (e.g. family, couple, friends) or professional (e.g. work colleagues, superior-inferior) social systems. Social anxiety indicates that an actual development task has not yet been accomplished and that socially anxious behavior, feelings and thoughts appear to be the best solution currently available. ST thus interprets social anxiety as an individual’s sensitive reaction when fearing being scrutinized and socially rejected. However, maintaining social system structures reciprocally maintains social anxiety [18, 19].

As we did not find a multi-person ST manual for treating specifically social anxiety disorders, JS and CH developed the first manualization of ST, integrating a broad range of systemic methods, for this type of disorder. We reviewed ST manuals for social anxiety disorders in child and adolescent psychotherapy [19] and well-established ST manuals for different disorders [20–22]. We used general ST concepts [18], integrating constructivist, solution-oriented [5, 23] and strategic [24–27] methods, in addition to attending disorder-specific relational ST dynamics [19, 28, 29]. According to the literature and our experiences of treating patients, the aim of ST is to contextualize symptoms of social anxiety by addressing an individual’s important private and/or professional social system. Social anxiety disorders indicate the disturbance of an entire social system and most if not all of its members. It does not rely on one single individual only. Consequently, the primary goal of ST is to identify and involve all important social system members. Thus, they will be invited to therapy sessions in addition to the individual patient. If they cannot attend physically, circular questions serve their inclusion into the room on a cognitive level. The analysis of transgenerational relationships, of past and present interpersonal interactions serve the development of a new understanding of the important roles, places and resources of all system members.

The systemic model of [name] and [name] [30] combines three different therapy settings with different participants in a multisystemic therapy concept. The first two therapies, and the majority of all therapy sessions alike, are individual but with a strong focus on relationship issues. They are combined with sessions with partners, parents or closest friends, and with one 3-hour group therapy session bringing together project patients and therapists. The ST manual differentiates between four phases which are described in detail in the method section.

### Efficacy

The efficacy of CBT for social anxiety disorders is well established [31]. A meta-analysis of 29 RCT studies showed a general effect size of 0.70 [32]. The largest German multicenter RCT investigating social anxiety disorders is the Social Phobia Psychotherapy Network (SOPHO-NET; *n* = 495) [18]. The SOPHO-NET was initiated by the lack of evidence for the efficacy of a new psychotherapy method for social anxiety disorders. In the SOPHO-NET, this was psychodynamic therapy (PD) which was compared to CBT. Based on the Liebowitz Social Anxiety Scale (LSAS), the authors investigated remission (LSAS score ≤30) and response (LSAS score reduction of at least 31 %) demonstrably comparable to an improvement of ≤2 in the Clinical Global Impression (CGI) [33]. The authors expected superiority of CBT with a small effect (Cohen’s *h* = 0.30; i.e. CBT response rate of 70 %, PD response rate of 55 %) [34]. With smaller effect than expected, results demonstrated superiority for remission (36 % CBT, 26 % PD; *h* = 0.22) but not for response (60 % CBT, 52 % PD) [35]. Again with small effect sizes, secondary interpersonal outcome measures such as the Inventory of Interpersonal Problems (IIP) [36] also showed significant differences in favor of CBT. At 6, 12 and 24 months after the end of treatment, significant between-group differences were no longer found in any outcome. Contrariwise, some other studies found that CBT patients tend to continue with problems in relationship formation after the end of therapy [37, 38].

Considering ST, we found only three RCTs for anxiety disorders [4–6], and only two of them investigated social anxiety disorders. One RCT (*n* = 120, Poland) compared 10 weeks of brief strategic therapy (BST) with MST. The outcome relied on the Interpersonal Sensitivity, Anxiety and Global Severity Index of the Symptom Checklist-90-R (SCL-90-R) [39, 40]. This trial demonstrated BST superiority for patients with social anxiety disorders only (response: 50 % BST, 20 % MST) but no significance of any treatment for patients with comorbid personality disorders (response: 7 % BST and MST) [6]. The second RCT (*n* = 83, Germany) compared a combined resource-oriented cognitive-behavioral therapy (ROCBT) with CBT. The main outcomes were the Social Interaction Anxiety Scale (SIAS) and Social Phobia Scale (SPS). SIAS and SPS are original German scales and were developed by the leading German CBT researcher for social anxiety disorders [41–43]. This trial demonstrated ROCBT superiority (Cohen’s *d* = 1.29, for both SIAS and SPS) compared to CBT (*d* = 0.86, for SIAS; *d* = 0.97, for SPS). Therapy effects were stable over the 2- and 10-year follow-up in both treatment conditions [5]. The third RCT (*n* = 326, Finland) compared long- and short-term PD with solution-focused ST. This study included patients with both mood and anxiety disorders. Results indicated a statistically significant reduction of symptoms on all outcomes in all three treatment groups during the 3-year study period, including the SCL-90-R anxiety subscale and the Hamilton Anxiety Rating Scale (HAM-A). Both instruments measure anxiety but not social anxiety [44]. The reduction was faster in short-term psychotherapies, including the solution-focused ST during the first year of follow-up. However, the reduction continued during the 3-year follow-up only for the long-term PD [4].

Consequently, none of the above described ST RCTs used the LSAS, though it is most often used for the assessment of social anxiety disorders [45]. The SOPHO-NET used the LSAS as the main outcome for that reason [35]. Willutzki and colleagues decided to use the original German SIAS and SPS, which highly correlate with the LSAS [5]. We therefore miss information regarding the efficacy of multi-person ST on established social anxiety assessments, such as the LSAS, SIAS and SPS. Additionally, we also miss information regarding the efficacy of multi-person ST when compared to a well-established comparator, the CBT.

### Pilot study

RCTs are regarded as the “gold standard” of present day evidence-based research in psychotherapy. They are often complex, time-consuming and expensive. Before a large RCT is undertaken, a pilot study should be conducted that mimics all the major essentials of the planned larger study [46]. As this study is the first trial that includes both a multi-person ST, integrating a broad range of systemic methods, and CBT, especially focusing on social anxiety disorders, we will have to conduct this pilot RCT before planning in detail the future main trial. Due to the mismatch of this study with previous investigations of ST for social anxiety disorders, reliable information that is needed for the sample size calculation for the main RCT is missing. Thus, this pilot study will help us to pay careful attention to sample size calculation, it will aim to save costs and use patients efficiently in the future RCT [47].

## Hypotheses

The main focus of this paper is to answer the question of what effect sizes of ST can be expected compared to CBT, to calculate how many patients will be needed to replicate effects indicated in this study. For that purpose, we descriptively and exploratively analyze the following hypotheses.**H1: Effects for social anxiety at the end of therapy (primary endpoint).** According to the SOPHO-NET [36] and the study by Willutzki and colleagues [5], we expect both CBT and ST to demonstrate a reduction of social anxiety symptoms, and that CBT will show a major change compared to the new ST.**H2: Effects for secondary outcomes at the end of therapy (primary endpoint).** According to the SOPHO-NET [36], we expect CBT to demonstrate a major change compared to the new ST on psychological functioning, social system and interpersonal functioning, symptom adjustment, and caregiver burden.**H3: Effects 9 and 12 months after the beginning of therapy (secondary and tertiary endpoint).** According to the SOPHO-NET [36] and the study by Knekt and colleagues [4], we expect both CBT and ST to show stable effects on primary and secondary outcomes during the follow-up period.

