## Methods

### Design and sample size

This pilot study is a prospective, open, interventive, balanced, bi-centric^1^, explorative RCT. The aim is to compare CBT and ST for social anxiety disorders. According to Cocks and Torgerson [47] for two-arm pilot studies of this kind, we will recruit 32 patients; 16 patients per CBT and ST, respectively (Fig. 1). Cocks and Torgerson used a confidence interval (CI) approach to calculate pilot sample sizes for continuous outcome measures. They supposed 0.3 of a standard deviation between two groups to be worthwhile, and stated that such a study would require 350 participants (assuming 80 % power and a two-sided alpha of 5 %). For pilot studies of which the primary goal is testing of the recruitment rate, they found 32 patients (approximately 9 % of the main sample size) to be required to produce a one-sided 80 % confidence limit. Cocks and Torgerson concluded that a pilot trial with that sample size, showed an estimate larger than zero and demonstrated feasibility to recruit and retain the patients, and so forth, should move forward with the main study.

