### Intervention

#### Manuals

The CBT manual [8] is well established. The goal is to establish a realistic self-perception. It includes: 1) generation of an idiosyncratic version of the disorder and identification of individual safety behaviors; 2) manipulation of self-focused attention and safety behaviors in role plays, and using video feedback to demonstrate their adverse effects; 3) training in attentional redeployment and reduction of safety behaviors through behavioral experiments (expositions), cognitive restructuring and changing of dysfunctional convictions; 4) relapse prevention; 5) booster sessions after the end of therapy to refresh therapeutic gains.

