#### Mixed-design ANOVA

We will perform mixed-design ANOVA to identify differences between treatment conditions [95]. Factors will be group (CBT or ST) and time (baseline, 8th, 15th, 20th therapy hour, end of therapy, respectively 26th therapy hour, 9 and 12 months after the beginning of therapy). Contrasts A will compare baseline with end of therapy. Contrasts B will indicate change between end of therapy, respectively 26th therapy hour, and 9 months after the beginning of therapy. Contrasts C will indicate change between end of therapy and 12 months after the beginning of therapy. We will control for differences in the length of treatment.

Time X Group interaction effect sizes will be assessed with partial eta-squared (η^2^) for the mixed-design ANOVA. Classification of effect sizes will be: η^2^ ≥ 0.01, small effect; η^2^ ≥ 0.06, medium effect; and η^2^ ≥ 0.14, large effect. Subsequently, for significant Time X Group interactions, simple effect analyses within and between groups will be performed [96]. Between-group effect sizes will be assessed with η^2^ and Cohen’s *d*. Classification of Cohen’s *d* will be: *d* ≥0.20, small effect; *d* ≥0.50, medium effect; and *d* ≥0.80, large effect [34]. In accordance with Coe [97], we will interpret Cohen’s *d* in terms of percentiles. Within-group effect sizes will be assessed with η^2^.

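### The significant-interaction condition on within-group analyses fits H3 poorly: per-arm follow-up change should be reported with an interval whatever the interaction shows

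*Protocol article*

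**What the plan says.** H3, in the Hypotheses section, reads "we expect both CBT and ST to show stable effects on primary and secondary outcomes during the follow-up period". The follow-up assessments are T6 and T7, at 9 and 12 months after the beginning of therapy. All three hypotheses are introduced with "For that purpose, we descriptively and exploratively analyze the following hypotheses".

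The Mixed-design ANOVA section sets up group by time with seven time levels, from baseline to 12 months. Contrasts B compare end of therapy with 9 months. For the later time point, "Contrasts C will indicate change between end of therapy and 12 months after the beginning of therapy". Neither is described as being computed separately in each arm. The section then says that "for significant Time X Group interactions, simple effect analyses within and between groups will be performed". Within-group effect sizes are to be expressed as eta-squared, and the text leaves open whether that sentence falls under the same condition.

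The opening of Statistical analyses plans descriptive measures, including confidence intervals, without any condition. It does not name an interval for change within an arm.

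On sample size, "we will recruit 32 patients; 16 patients per CBT and ST, respectively".

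**The concern.** H3 is a no-change statement about CBT and about ST. To examine it, one needs the change from end of therapy to follow-up in each arm, with its direction and its uncertainty. The stated rule opens the within-group analysis only when the arms differ in their course. A similar course in both arms contributes nothing to the interaction over follow-up, so the rule tends to close the analysis where H3 is right. It also closes it where both arms relapse together.

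H1 is affected in the same way. Its first part expects symptoms to fall in both arms, which is again a within-arm statement and does not depend on an interaction.

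At stake is what the pilot can say about durability. If the within-arm results are withheld, the report may have little beyond non-significant tests to put against H3. At this sample size such tests say little.

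**Working it through.** **The plan's own figures.** The Design and sample size section takes 0.3 SD between groups as worthwhile, "assuming 80 % power and a two-sided alpha of 5" %, and gives 350 patients for a main trial.
- Main trial: n per arm = 2 × ((1.960 + 0.842)/0.3)² ≈ 174.4, rounded up to 175, so 350 in total.
- Pilot, one-sided 80% limit: n per arm = 2 × (0.842/0.3)² = 15.74, rounded up to 16, so 32 in total. 32/350 = 9.1%.

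Both stated figures reproduce. They concern a between-group difference and do not address H3.

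**Does an unconditional item supply what H3 needs?**
- Contrasts B and C are not stated to be conditional, but also not stated to be per arm. A contrast averaged over arms halves a relapse confined to one arm.
- Eta-squared carries no sign, so it cannot separate relapse from further improvement.
- The descriptive intervals are unspecified. Separate intervals at end of therapy and at 12 months do not give the interval for the paired change.

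**Precision of a within-arm change.** Inputs: 16 per arm (protocol), full retention (assumed), correlation r between end of therapy and follow-up (not in the protocol; 0.5 to 0.8 assumed). In units of the outcome SD, the SD of change is √(2(1 − r)). The 95% half-width is t(0.975, 15 df) × SD of change/√16, with t = 2.131.

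| r | SD of change | SE | 95% half-width |
|---|---|---|---|
| 0.5 | 1.000 | 0.250 | 0.53 |
| 0.7 | 0.775 | 0.194 | 0.41 |
| 0.8 | 0.632 | 0.158 | 0.34 |

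**What significance tests would show.** I use a worsening of 0.3 SD as an illustration. The number comes from "They supposed 0.3 of a standard deviation between two groups to be worthwhile", which is a between-group figure and not a relapse margin. Tests are two-sided at 5%, with power from the noncentral t distribution.
- Within one arm: noncentrality 0.3 × √16/SD of change = 1.20, 1.55, 1.90.
- Interaction contrast on follow-up change, only one arm worsening: noncentrality 0.3 × √(16/2)/SD of change = 0.85, 1.10, 1.34 (30 df).
- Both arms worsening equally, contrast pooled over 32 patients: noncentrality 0.3 × √32/SD of change = 1.70, 2.19, 2.68 (30 df).

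| r | Within one arm: not significant | Interaction, one arm worsens: significant | Pooled, both arms worsen: not significant |
|---|---|---|---|
| 0.5 | 80% | 13% | 62% |
| 0.7 | 69% | 19% | 44% |
| 0.8 | 57% | 25% | 26% |

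If the arms change alike over follow-up, a follow-up interaction contrast is significant in about 5% of trials, by chance alone. For a larger within-arm worsening of 0.5 SD, the non-significant share is 53%, 32% and 16%.

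**The case against.** A reader might infer that the plan will call effects stable whenever contrasts B and C are non-significant. No passage says so. The contrasts are described as indicating change, and all statistics are declared descriptive and explorative.

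A reader might also infer that within-arm change will never be analysed, or that the plan cannot support H3 at all. That goes too far. Contrasts B and C and the descriptive confidence intervals are not tied to the interaction, and the eta-squared sentence is ambiguous. Nor is the condition bound to stay closed under H3. The interaction spans seven time points, and H1 expects CBT to change more than ST by end of therapy, so a difference arising before follow-up could open it. This objection stands against the stronger readings. It does not rescue the rule, because an interaction produced during therapy says nothing about the period H3 concerns.

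It would likewise be wrong to say that a real relapse is more likely than not to pass as stability. That would require the unstated decision rule, and the share depends on the size of the relapse, the correlation and the contrast used. A common 0.3 SD worsening tested by a pooled contrast is missed in fewer than half of trials at r = 0.7 and 0.8.

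Low power is inherent in a pilot and is acknowledged: the Biases and limitations section reserves any confirmatory statement on efficacy for the main trial. A numerical margin for stability may properly sit in a fuller document, so its absence from the article is not the point here. What remains is a stated rule that does not match the hypothesis.

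**Conclusion.** The concern holds in a limited form. The interaction condition on within-group simple effects fits H3, and the both-arms-improve part of H1, poorly. The unconditional items do not clearly supply a signed change per arm with an interval. With 16 per arm, the 95% interval for that change is roughly ±0.34 to ±0.53 SD, so non-significance would be weak evidence of stability. If one arm alone worsened by 0.3 SD, a follow-up interaction contrast would be significant in only about 13 to 25% of trials.

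These figures rest on full retention and an assumed correlation of 0.5 to 0.8; losses would widen the intervals. The 0.3 SD is illustrative. Severity is minor to moderate: H3 is exploratory and concerns the secondary and tertiary endpoints.

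A separate side point concerns the follow-up window. The Abstract limits therapy to 26 hours, and the Therapy (T1 to T5) section sets T5 at the end of therapy or of those 26 hours. The Manuals section lists, for CBT, "booster sessions after the end of therapy to refresh therapeutic gains", with a corresponding phase for ST. The article does not date these sessions or say whether they count toward the limit, so it cannot be concluded that they fall between T5 and T7. Equally, that window cannot yet be described as treatment-free.

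**What to change.** 1. Remove the interaction condition for within-arm change. Report the change from T5 to T6 and from T5 to T7 in each arm, with its sign and a confidence interval, whatever the interaction p-value. Report baseline-to-T5 change per arm in the same way for H1.
2. Say that contrasts B and C will be given per arm as well as between arms.
3. Describe an effect as stable only as far as the interval excludes a worsening judged relevant in advance. The size of that worsening is the sponsor's choice. State that non-significance will not be taken as stability.
4. Reconcile the passages on the 26-hour limit, the definition of T5 and the booster sessions before T5 to T7 is described as treatment-free.

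The cost is a few sentences in the analysis plan, with no extra patients or assessments. The downside is that the pilot may have to report that stability was not determined. With intervals of this width, that is a realistic outcome.
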